## Abstract

**Background:**

Most breast cancer patients with non-metastatic disease receive adjuvant local or loco-regional radiotherapy. To be scheduled for irradiation may cause distress and fears that can lead to sleep disorders. Few reports focused on sleep problems in patients assigned to radiotherapy. This study evaluates the course of sleep disorders during adjuvant radiotherapy for primary breast cancer and potential risk factors including the use of smartphones or tablets at bedtime.

**Methods:**

The main goal is the evaluation of sleep disorders prior to radiotherapy and after 15 fractions of radiotherapy. A potential effect of habituation to the procedure of radiotherapy can be assumed that will likely lead to improvement (decrease) of sleep disorders. Improvement of sleep disorders (compared to baseline before radiotherapy) is defined as decrease of the severity of sleep disorders by ≥2 points on a patient self-rating scale (0 = no problems; 10 = maximum problems) or decrease of distress caused by sleep disorders by ≥2 points on a self-rating scale (0 = no distress; 10 = maximum distress) or reduction of the dose of sleeping drugs by ≥25%. Additional endpoints include sleep disorders after 5 fractions and at the end of radiotherapy. Moreover, potential risk factors including the use of smartphones or tablets at bedtime are evaluated. Fifty-one patients (48 plus potential drop-outs) are required. With this sample size, a one-sample binomial test with a one-sided significance level of 2.5% has a power of 80% to yield statistical significance, if the rate of patients with improvement of sleep disorders is 25% (rate under the alternative hypothesis) and assuming that a decrease of ≤10% has to be judged as a random, non-causal change in this uncontrolled study setting (null hypothesis).

**Discussion:**

If a decrease of sleep disorders during the course of radiotherapy is shown, this aspect should be included in the pre-radiotherapy consent discussion with the patients. Moreover, identification of additional risk factors will likely lead to earlier psychological support. If the use of smartphones or tablets at bedtime is a risk factor, patients should be advised to change this behavior.

**Trial registration:**

clinicaltrials.gov (NCT04879264; URL: https://clinicaltrials.gov/show/NCT04879264); registered on 7th of May, 2021.

## Background

Breast cancer is one of the most common cancer types in Europe and Northern America [1]. Most of the patients with non-metastatic disease receive adjuvant radiotherapy of the breast or the chest wall [2]. If specific risk factors exist, irradiation may be also indicated for loco-regional lymph nodes. The situation that a breast cancer patient is scheduled for radiotherapy may cause distress due to a sense of menace in view of the technology as well as fear of radiation in general and potential side effects of the planned treatment. A potential consequence of distress and fears can be sleep disorders. Very few studies were published so far that particularly focused on sleep disorders before and during a course of radiation therapy [3.5]. The prevalence of sleep disorders prior to adjuvant radiotherapy for breast cancer ranged between 45 and 48% [3, 4]. Conflicting results were reported regarding sleep disorders during a course of radiotherapy. In a study of breast cancer and prostate cancer patients receiving radiotherapy, sleep disorders occurred mainly before the start of treatment and during the first radiation fractions [5]. Patients appeared to have developed coping strategies during the course of treatment leading to improvement of their sleep disorders. However, in another study of patients with breast or prostate cancer, the patients reported an increase of insomnia during the course of radiotherapy as a result of treatment-related toxicities [6].

This demonstrates that additional studies are required that investigate sleep disorders in breast cancer and prostate cancer patients scheduled for irradiation. If sleep disorders increase during a course of radiotherapy, it is important to identify these patients as soon as possible to be able to offer them early psychological support. Therefore, the knowledge of corresponding risk factors is also very important [4]. If sleep disorders decrease during the course of treatment, radiation oncologists can address this finding and reassure the patients during the informed consent discussion prior to the treatment. In both situations, the patients will benefit from additional studies. The present study evaluates the course of sleep disorders during adjuvant radiotherapy for primary breast cancer and additional potential risk factors.

## Methods and design

This single-arm prospective interventional study conducted at an academic center in Northern Germany investigates sleep disorders prior to and during a course of adjuvant radiotherapy for primary breast cancer. It achieved approval from the ethics committee of the University of Lübeck (reference 21–137) and was registered at clinicaltrials.gov (identifier: NCT04879264).

## Objectives and endpoints

The primary goal of the study is to evaluate sleep disorders in breast cancer patients prior to and during (after 15 fractions/3 weeks) a course of radiotherapy in terms of severity of sleep disorders, distress for the patients and intake of sleeping drugs. These data are used to evaluate the potential effect of habituation to the procedure of radiotherapy and generate hypotheses. Habituation to radiotherapy will likely lead to an improvement (decrease) of sleep disorders during the course of radiotherapy when compared to baseline (prior to radiotherapy). Improvement of sleep disorders is defined as decrease of severity of sleep disorders by at least 2 points on a patient self-rating scale (0 = no problems; 10 = maximum problems) or decrease of distress caused by sleep disorders by at least 2 points on a patient self-rating scale (0 = no distress; 10 = maximum distress) or reduction of the dose of sleeping drugs by ≥25%. The criterion regarding the intake of sleeping drugs was chosen according to another situation of radiotherapy, namely irradiation of painful bone metastases [7]. To obtain the data for these three criteria, patients will complete questionnaires including two self-rating scales and information about intake and doses of sleeping drugs. Additional endpoints include sleep disorders after 5 fractions of radiotherapy, sleep disorders at the end of the radiotherapy course. Moreover, potential risk factors for sleep disorders including the impact of the use of smartphones or tablets at bedtime will be evaluated [3, 4, 8].

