### Interventions

Patients receive the same standard radiotherapy for breast cancer following breast-conserving surgery or mastectomy as they would have received without participation in this study. If necessary, any medical care and interventions are permitted during the study.

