### Statistical methods for investigated endpoints

The efficacy analysis will be performed on the modified Full Analysis Set defined as all patients receiving radiotherapy with a completed questionnaire at baseline and at least one completed questionnaire after start of treatment. Similar to a previous study, the statistical analyses are mainly descriptive and exploratory [10]. Sleep disorders at baseline and during radiotherapy will be rated using two patient self-reporting scales (sleep disorders and distress) and intake of sleeping drugs. To evaluate the rate of patients with decrease of sleep disorders after 15 fractions of radiotherapy (generally at the end of the third week of treatment), the dichotomized composite endpoint (decrease of severity of sleep disorders, decrease of distress caused by sleep disorders, reduction of the dose of sleeping drugs) is considered, even if patients discontinue radiotherapy prematurely (treatment policy estimand). The number of missing data will be reported. The point estimate of the rate of decrease and the associated 95% confidence interval will be presented. To test whether the rate of decrease is significantly > 10%, the one-sided binomial test at a one-sided 2.5% significance level will be applied.

To further assess the impact of other factors on the primary endpoint, stratified analyses will be conducted. Factors of particular interest include sleep disorders at baseline and use of smartphones or tablets at bedtime. Furthermore, a logistic regression model including the sleep disorder rating scale at baseline, use of smartphones or tablets at bedtime and other factors such as age, type of breast surgery, systemic anticancer treatment, body mass index and co-morbidity will be fitted to identify significant predictive factors for decrease of sleep disorders. Adjusted odds ratios and 95% confidence interval (Wald χ2) will be derived.

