In addition, each component of the primary endpoint will be subjected to statistical analyses to evaluate sleep disorders during the study using descriptive statistical methods. These analyses allow detailed assessments of the scales over time considering potential decrease and increase in sleep disorders. For graphical visualization, Spaghetti-plots and Box-Whisker diagrams will be provided. Changes from baseline will be considered and subjected to descriptive analyses. Friedman and Wilcoxon-signed rank tests may be applied to compare study visits. Cumulative distribution plots of changes from baseline at each visit will be presented; they display a continuous change from baseline on x-axis and the cumulative percentage of patients experiencing that change on y-axis. Analyses will be further stratified by sleeping disorders at baseline and use of smartphones at bedtime. For further exploratory analysis, rates of patients experiencing sleep disorders at each time will be estimated together with associated confidence intervals. These analyses will also be stratified by sleeping disorders at baseline and the use of smartphones at bedtime.

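### The primary responder rule accepts improvement on any one component, ignores worsening on the others, and ignores sleeping drugs that were started or increased, so some counted responders are no evidence of habituation

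*Protocol article*

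**What the plan says.** The Objectives and endpoints section of the protocol article gives the responder rule in full, and the Abstract repeats it. It has three parts, and any one suffices:

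- severity: "Improvement of sleep disorders is defined as decrease of severity of sleep disorders by at least 2 points on a patient self-rating scale";
- distress: "or decrease of distress caused by sleep disorders by at least 2 points on a patient self-rating scale";
- sleeping drugs: "or reduction of the dose of sleeping drugs by ≥25" per cent.

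The same section gives the purpose: "These data are used to evaluate the potential effect of habituation to the procedure of radiotherapy and generate hypotheses".

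The section on statistical methods carries the rule into the primary test as "the dichotomized composite endpoint (decrease of severity of sleep disorders, decrease of distress caused by sleep disorders, reduction of the dose of sleeping drugs"), evaluated after 15 fractions and compared with 10% at a one-sided 2.5% level. The only intercurrent event it names is early stopping of radiotherapy: the endpoint "is considered, even if patients discontinue radiotherapy prematurely (treatment policy estimand").

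The Interventions section states: "If necessary, any medical care and interventions are permitted during the study".

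No section makes response conditional on the other components not worsening, or on sleeping drugs not being started or increased.

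**The concern.** The rule looks only for improvement. Taken literally, each of these patients is a responder:

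- (a) severity falls from 6 to 4 after a sleeping drug was started or its dose raised;
- (b) the sleeping-drug dose is cut by 25% while severity rises from 4 to 8;
- (c) distress falls by 2 points while severity rises by 4.

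None of them is evidence that the patient became used to radiotherapy. Drug intake is treated as part of the outcome in one direction only: less drug is a success, more drug is invisible. Worsening is a real possibility here, because the Background cites one study in which insomnia increased during radiotherapy.

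All these classifications push the same way, towards a higher rate and a significant result. The Discussion intends to bring a demonstrated decrease into the consent conversation with patients, so the meaning of a responder matters even in a mainly exploratory study.

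**Working it through.** **1. The plan's own figures.** Inputs from Sample size calculations: n = 48 analysed, null rate 10%, alternative 25%, exact one-sided binomial test at 2.5%, 5% loss. With X ~ Binomial(48, p), the critical value is the smallest r with P(X ≥ r | p = 0.10) ≤ 0.025.

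- P(X ≥ 9 | 0.10) = 0.0463, too large.
- P(X ≥ 10 | 0.10) = 0.0187, so rejection needs at least 10 of 48 (10/48 = 20.8%).
- Power: P(X ≥ 10 | 0.25) = 0.795 and P(X ≥ 10 | 0.28) = 0.901.
- Enrolment: 48/0.95 = 50.5, rounded up to 51.

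The stated 80%, 90% and 51 all reproduce. The calculation is sound; the issue is who counts in X.

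**2. Effect of extra responders.** The documents give no rate of drug changes or of opposite moves, so the added share q is an assumption. If the rate would otherwise be 10%, the rejection probability is P(X ≥ 10 | 0.10 + q):

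| q (assumed) | patients of 48 | P(reject) |
|---|---|---|
| 0 | 0 | 1.9% |
| 3 points | 0.03 × 48 = 1.4 | 8.7% |
| 5 points | 0.05 × 48 = 2.4 | 17.4% |

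One to three patients are enough to move the test noticeably.

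**3. How often the two scales move in opposite directions.** This was simulated with two rounded change scores, zero mean change, an SD of change of 1 to 2.5 and a correlation of 0.3 to 0.9. All of these are assumptions, since the documents give none of them.

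- Down by at least 2 on one scale and up by at least 2 on the other: 0% to 9% of patients, and close to 0% at correlation 0.9.
- Responders on one scale alone: 7% to 27%.
- Responders on either scale: 9% to 44%.
- Responders on either scale with no rise of at least 2 on the other: 9% to 36%.

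Much of the gap between one scale and either scale comes from having two chances to respond, not from opposite moves. Pattern (c) is therefore likely to be a minor contributor, which leaves drug changes as the main route.

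**4. Cost in power of a stricter primary rule.** A net rule can only lower the responder rate. With n = 48 and 10 responders still required:

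- 25%: power 79.5%
- 23%: power 69%
- 22%: power 63%

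**The case against.** Several counter-arguments carry weight.

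- **The cause is not only the 'or'.** Pattern (a) would also count under an endpoint using severity alone. It comes from uncontrolled concomitant medication. This stands; only (b) and (c) arise from combining components. Still, this endpoint measures drug intake and then uses it in one direction only, so the gap lies within its own definition.
- **The 10% null may absorb part of it.** The sample size section sets 10% as non-causal change in an uncontrolled setting. This stands in part: stacking q on top of 10% assumes that none of it is already covered. However, the 10% is not derived for a three-way rule or linked to drug changes.
- **Components are reported separately.** The statistical section says that "each component of the primary endpoint will be subjected to statistical analyses to evaluate sleep disorders during the study using descriptive statistical methods", covering increases as well as decreases. Deterioration would therefore be visible, but no patient's responder status changes.
- **Treatment policy covers new drugs.** The text applies that strategy only to premature discontinuation of radiotherapy. Extending it would turn the question into improvement under any care, which is not the stated aim.
- **It is exploratory, and detail may sit in an unseen plan.** The analyses are called mainly descriptive and exploratory, which lowers the stakes. But the responder rule is stated completely here and is tested formally, so this is not simply omitted detail.

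A reader might infer that the test's true false-positive rate is 17% or more, or that the composite is invalid. The documents support neither: q has no source in them, and the overlap with the 10% allowance is unknown.

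**Conclusion.** The point holds as a weakness in the definition of the primary endpoint. The stated rule classifies as improved some patients who worsened on another component or whose sleeping drugs were started or increased. These errors act in one direction, towards rejecting 10%.

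The size cannot be determined from the documents. A rise in rejection probability from 1.9% to between 8.7% and 17% rests on two assumptions: that 3 to 5 percentage points of patients respond only by these routes, and that the 10% null covers none of them. The real effect could be smaller.

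No responder rule can isolate habituation in a single-arm study. A net rule would still count regression to the mean or recovery after surgery. What it removes is a misclassification that the study's own data can detect. This is a cheap improvement that should be made; the documents do not support calling it a must-fix.

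**What to change.** Before data are analysed, and for classification only (it has no bearing on any patient's care), define net improvement as either:

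- severity or distress down by at least 2 points, with no rise of at least 2 on the other scale and no sleeping drug started or increased by at least 25%; or
- sleeping-drug dose down by at least 25%, with no rise of at least 2 on either scale.

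**Preferred:** make this the primary definition, keep the current any-component rule as a sensitivity analysis, and restate power, with the 10% and 25% rates justified for the new definition.

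**Minimum:** keep the current primary rule, prespecify net improvement as a key sensitivity analysis, show its rate and 95% confidence interval beside the primary result, and base any conclusion about habituation on both.

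**Cost:** no new data, since both scales and the type and dose of sleeping drugs are already on the questionnaire. The observed rate will be the same or somewhat lower. If the net rule becomes primary, power at 48 patients falls (79.5% at a 25% rate, 69% at 23%, 63% at 22%), and the article says the sample size is already the maximum achievable. The minimum option leaves the primary test and its power unchanged.

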### Eligibility criteria

Inclusion criteria include female gender, histologically proven breast cancer, indication for radiotherapy, sleep disorders (at least 2 points on the sleep disorder self-rating scale), Eastern Cooperative Oncology Group (ECOG) performance score of 0–2, age ≥ 18 years, written informed consent, and capacity of the patient to cooperate (including the ability to complete a questionnaire). Exclusion criteria are pregnancy or lactation and limited legal capacity or being under legal supervision.

### Assessments

Parameters assessed prior to radiotherapy include demographics (age, date of birth, gender), medical history, concomitant diseases, physical/practical and emotional problems including depression and anxiety, concomitant medication including sleeping drugs and anticancer treatment, physical examination, histology, upfront surgery, and upfront systemic therapy. The following parameters will be assessed during the course of the study (Fig. 1):Sleep disorders

**Fig. 1 Fig1:**
[figure not shown]
Timeline of enrolment, interventions and assessments of the RADIO-SLEEP study

Sleep disorders will be assessed prior to radiotherapy (baseline), and during (after 5 and 15 fractions) and at the end of the radiotherapy course. Evaluation is based on questionnaires including self-rating scales regarding severity and distress due to sleep disorders and information regarding the intake of sleeping drugs. Moreover, the use of smartphones and tablets at bedtime and other factors such as age, type of breast surgery, physical/practical and emotional problems including depression and anxiety, systemic anticancer treatment, side effects of radiotherapy, body mass index, co-morbidity and other factors causing distress will be correlated to sleep disorders [3, 4, 8].2.Adverse Events.

Adverse events will be assessed on an ongoing basis according to Common Terminology Criteria for Adverse Events (CTCAE) version 5.0 [9].

### Interventions

Patients receive the same standard radiotherapy for breast cancer following breast-conserving surgery or mastectomy as they would have received without participation in this study. If necessary, any medical care and interventions are permitted during the study.

### Radiotherapy for breast cancer

Most breast cancer patients receive breast-conserving surgery followed by whole-breast irradiation with 40 Gy of hypo-fractionated radiotherapy (5 × 2.667 Gy per week) or 50.4 Gy of conventional fractionation (5 × 1.8 Gy per week) [2]. Patients younger than 51 years and those older than 50 years with increased risk of developing a local recurrence receive a boost of 5 × 2.0 Gy to the tumor bed. After mastectomy, radiotherapy of the chest wall is indicated in the following situations: pT4 or pT3 pN0 R0 and risk factors, incomplete resection without re-resection, involvement of > 3 axillary lymph nodes, involvement of 1–3 axillary lymph nodes plus risk factors [2]. In addition to whole-breast irradiation, radiotherapy of loco-regional lymph nodes is recommended for involvement of > 3 axillary lymph nodes and for involvement of 1–3 axillary lymph nodes plus risk factors. If the treatment volume includes lymph nodes, the preferred dose-fractionation regimen is 50.4 Gy in 28 fractions of 1.8 Gy [2].

### Possible acute side effects of radiotherapy

Radiotherapy can be associated with side effects such as dermatitis, breast edema, esophagitis, pneumonitis, cardia arrhythmia, hypothyroidism, loss of appetite, nausea/vomiting, fatigue and pancytopenia. In case of a grade 3 toxicity according to CTCAE criteria version 5.0 [9], radiotherapy may be delayed for up to 7 days without consequences. If it is delayed for more than 7 days, the coordinating physician of the study must be informed.

### Questionnaires

The patients will be asked to complete a questionnaire prior to radiotherapy, after 5 and 15 fractions of radiotherapy, and at the end of their radiotherapy course (which may be also after 15 fractions). The questionnaire, which is available in full in German only, includes three questions regarding health and general well-being, ten questions regarding distress in everyday life during the last week, and 16 questions regarding symptoms and discomfort during the last week including sleep disorders. In case of sleep disorders, the patients are asked to complete a self-rating scale regarding the severity of their sleep disorders ranging from 0 to 10 (0 = no problems; 10 = maximum problems) and another self-rating scale regarding the distress caused by the sleep disorders also ranging from 0 to 10 (0 = no distress; 10 = maximum distress). In addition, the patients are asked to indicate whether they use sleeping drugs and, if applicable, the type and dose of these drugs. In addition, the patients are asked to answer three general questions regarding their sleep disorders (type of sleep disorders, impact on daily life, and reaction of their social environment). Moreover, the patients who use smartphones or tablets are asked to answer 11 questions regarding the use of these devices in general and at bedtime.

### Sample size calculations

The main goal of the study is to evaluate sleep disorders in breast cancer patients prior to and during a course of radiotherapy in terms of severity of sleep disorders, distress caused by sleep disorders and use of sleeping drugs. This will allow to evaluate the potential effect of habituation to radiotherapy during the course of treatment and generate hypotheses. Forty-eight patients with documented start of radiotherapy, a documented completed questionnaire at baseline, and at least one completed questionnaire during radiotherapy are subjected to statistical analysis. Assuming that 5% of patients do not fulfil the requirements, 51 patients should be enrolled. This sample size is set at the maximum that is deemed achievable in this study within the timeframe given the size of the target population.

With this sample size, a one-sided exact test for one binomial population with a significance level of 2.5% has a power of 80% to yield statistical significance if the rate of patients with improvement (decrease) of sleep disorders during the radiotherapy compared to baseline is 25% (rate under the alternative hypothesis) and specifying a decrease of 10% as non-causal change in this uncontrolled study setting (null hypothesis). With an improvement rate of at least 28% under the alternative hypothesis, the statistical test with this sample size achieves a power of at least 90% (calculated with StatXact, Version 11, Statistical software for exact nonparametric inference, Cytel Software, Cambridge, MA, USA).

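### The stated power holds only if 48 to 50 patients have a 15-fraction outcome, but the 48 are counted by any one on-treatment questionnaire

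*Protocol article*

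**What the plan says.** All references are to the protocol article.

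- **Sample size calculations.** The 48 are patients who started radiotherapy and have "a documented completed questionnaire at baseline, and at least one completed questionnaire during radiotherapy are subjected to statistical analysis". The loss allowance refers to the same requirements: "Assuming that 5% of patients do not fulfil the requirements, 51 patients should be enrolled". The test is a one-sided exact binomial test at 2.5% against a 10% null rate. The stated power is 80% for a true improvement rate of 25% and at least 90% for 28% or more. The section adds that the sample is the largest thought achievable.
- **Statistical methods for investigated endpoints.** The modified Full Analysis Set uses the same any-visit rule. The primary analysis is tied to one visit: "To evaluate the rate of patients with decrease of sleep disorders after 15 fractions of radiotherapy". On missing outcomes the article says only "The number of missing data will be reported". Early stopping of radiotherapy does not remove a patient (treatment policy estimand).
- **Questionnaires.** Forms are due at baseline, after 5 fractions, after 15 fractions and at the end of the course. The last two can coincide.
- **Discussion.** The comparison of 15 fractions with baseline is named the primary endpoint.
- **Abstract, Methods.** The power statement follows directly on the enrolment number: "Fifty-one patients (48 plus potential drop-outs) are required. With this sample size".

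**The concern.** The count behind the power and the outcome being tested rest on different rules. One on-treatment form from any visit makes a patient count among the 48, but only the 15-fraction assessment supplies the primary outcome. The 5% is used up by patients who fail the any-visit rule, so nothing is set aside for patients who pass it and still lack the 15-fraction form.

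This matters because the exact test at 48 only just reaches its stated figures. The wording about sample size adds some ambiguity: in both the abstract and the sample size section, the power sentence follows a mention of 51, and 51 analysed patients do not give the stated power either. At stake is the power quoted for the trial's one formal hypothesis test.

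**Working it through.** **Inputs.** Null rate 10%, alternative rates 25% and 28%, one-sided level 2.5%, 48 analysed, 5% allowance, 51 enrolled (all from Sample size calculations). No 15-fraction missing rate is given, so any such rate below is an assumption.

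**Formula.** For n observed outcomes, let c be the smallest integer with P(X ≥ c | n, 0.10) ≤ 0.025. Power is P(X ≥ c | n, p), with X binomial and p = 0.25 or 0.28.

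**Step 1: the plan's own figures.** At n = 48, P(X ≥ 9 | 48, 0.10) = 0.0463 is too large and P(X ≥ 10 | 48, 0.10) = 0.0187 is allowed, so c = 10. Power is 79.5% at 25% and 90.05% at 28%. Enrolment is 48 / 0.95 = 50.5, rounded up to 51. The stated 80%, 90% and 51 all reproduce.

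**Step 2: other numbers of observed 15-fraction outcomes.**

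| Observed n | c | Actual level | Power at 25% | Power at 28% |
|---|---|---|---|---|
| 51 | 11 | 0.0109 | 76.2% | 88.3% |
| 50 | 10 | 0.0245 | 83.6% | 92.6% |
| 49 | 10 | 0.0215 | 81.7% | 91.4% |
| 48 | 10 | 0.0187 | 79.5% | 90.05% |
| 47 | 10 | 0.0163 | 77.2% | 88.5% |
| 46 | 10 | 0.0140 | 74.7% | 86.8% |
| 45 | 10 | 0.0120 | 72.0% | 84.9% |
| 44 | 10 | 0.0103 | 69.1% | 82.8% |
| 43 | 9 | 0.0244 | 78.3% | 88.8% |

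The pattern is saw-toothed. Power jumps when c changes, so the loss does not grow steadily when only observed outcomes are analysed. Still, no n from 40 to 47 reaches 80% or 90%.

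**Step 3: does the handling rule matter?** Take a set of 48 of whom 44 to 47 are observed. Leaving the missing patients out gives c = 10. Keeping them in the denominator as not improved also gives c = 10. Power is therefore the same under both rules, and choosing between them does not restore the stated figures. The rules diverge from 43 observed downwards.

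**Step 4: average power if a share q of the 48 lacks the 15-fraction form at random (assumed q).** When missing patients are left out, power is averaged over n ~ Binomial(48, 1 − q). When they count as not improved, power is P(X ≥ 10 | 48, p(1 − q)).

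| q | Chance of at least one missing, 1 − (1 − q)^48 | Left out: 25% / 28% | Not improved: 25% / 28% |
|---|---|---|---|
| 2% | 62% | 77.2% / 88.5% | 77.2% / 88.5% |
| 5% | 91% | 74.6% / 86.6% | 73.4% / 85.8% |
| 10% | 99% | 73.3% / 85.5% | 66.4% / 80.4% |

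**Step 5: starting from 51 enrolled.** If 5% of the 51 are lost in total, at random, average power with observed outcomes only is 79.7% and 90.1%. If a further 5% of the remainder lack the 15-fraction form, it is 75.8% and 87.5%.

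**The case against.** The strongest reply is that nothing has been miscalculated. The power and the step from 48 to 51 are right, and the number analysed is whoever qualifies out of 51, not exactly 48. If only one or two of the 51 lack the 15-fraction outcome for any reason, power is above the stated figures. If the total loss averages 5%, power is about as stated. For patients whose course ends at 15 fractions, the end-of-course form is the 15-fraction form. The article names 48 as the number analysed, so the stated power is most naturally read as belonging to 48. The fall at 51 comes from the discreteness of the test. The analyses are described as mainly descriptive and exploratory, and the rule for missing outcomes may be in the SAP, which is not available here.

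Most of this stands. It rules out the reading that the stated power is simply not delivered: that would need a missing rate the article does not give. It also disposes of a second inference a reader might draw, that the 2.5% level is exceeded. If five of 48 were missing, all were non-improvers and all were left out, 9 of 43 would suffice and the error would be P(X ≥ 9 | 48, 0.10) = 4.6%. That is a worst case, under a handling rule that the article never prescribes.

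What the reply does not remove is the mismatch itself. The evaluability rule, the 5% and the power statement are all fixed in this article, and they do not refer to the visit that is tested. The exploratory label does not settle it either, since the same section specifies a formal test at 2.5%.

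**Conclusion.** The point holds in a conditional form. With 51 enrolled, the stated power is right if 48 to 50 patients contribute a 15-fraction outcome (taking 79.5% as 80%), and the plan's own counting rule does not secure that number. From 48 down to 44 observed, each further missing outcome costs about 2 to 3 percentage points at a 25% rate. The 90% figure at 28% fails with the first one. Full retention of 51 also misses both figures, at 76.2% and 88.3%.

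The size of the actual shortfall is unknown. It rests on an assumed 15-fraction missing rate: at 5% of the 48, power at 25% is about 73% to 75%. The finding is a gap between definition and power statement, not an arithmetic error, and it does not show that the test is invalid.

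**What to change.** In Sample size calculations and in the Methods part of the Abstract:

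1. Define the 48, and the 5% allowance, by patients with both a baseline and a 15-fraction outcome. This concerns the planning count. The modified Full Analysis Set need not change.
2. Say that the power refers to 48 analysed patients, not to 51.
3. State the power as conditional on that number: 79.5% at 25% and 90% at 28% with 48 observed, together with the values for 44 to 47 and for 51 from the table above.

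If the SAP counts a missing outcome as not improved, the power has to be computed with the whole modified Full Analysis Set as denominator, because the figures by number observed no longer apply. For example, with 51 in the set and 48 observed, 11 improvers are needed and power at 25% is P(X ≥ 11 | 48, 0.25) = 68.4%, not 79.5%.

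The cost is wording and a slightly less favourable stated power. No extra patients are needed. Covering a further 5% loss by enrolment would take 48 / (0.95 × 0.95) = 53.2, so 54 patients, which is above the number the article calls achievable. Restating the power is therefore the realistic course.
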